### Analysis strategy

#### Primary analyses of efficacy

Sick leave/insurance status will be calculated as risks of shifting between different states of sick leave, disability pension, and recovered. The outcome from the participating clinics will be combined if no gross center effect is found. The analyses will follow the "intention to treat" principle. Per protocol analysis will also be performed. The proportions of participants with a positive primary outcome will also be compared across the treatment groups. If there are significant differences, we will estimate the number of participants that need to be treated in order for one additional participant to benefit (NNT), compared to the least effective therapy. A Cox-proportional hazards model may model the transitions between the different states. Regression models for the transition probabilities will also be performed. Explanatory variables (treatment) and confounders (e.g. age, gender) will be included as in any regression model. Possible changes in diagnosis and other characteristics will be built in. Partial recovery represented by partial sick leave will be accounted for.

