### Randomization

The patients will be randomized, using concealed randomization, to one of the following four treatments; 1) BI only, 2) BI and CBT, 3) BI and seal oil, or 4) BI and soy oil. This is done according to a computer generated randomization list, generated by the trial statistician. The list is stratified by clinic and gender. A central telephone randomization system, as already set up by our research unit will be used. At each of the participating clinics, a research assistant that is not involved in the treatment calls the research unit (Uni Health) to get information on which treatment the patient is randomized to. The research unit receives information about the patient's id number, gender, age, and diagnoses before the treatment allocation is disclosed, ensuring that the sequence is concealed until the intervention is assigned. The allocation code, including details of block size etc. will not be revealed to the researchers or the clinicians until recruitment, data collection, and laboratory analyses are complete. For those patients allocated to nutritional supplementation, the clinics provide blinded boxes, containing capsules with either seal oil or soy oil. All researchers, clinicians, and participants are blinded to treatment allocation of individual participants for the nutritional supplementation. Researchers at Uni Health, the trial statistician, and those assessing the main outcome of the study will be blinded to group assignment. Patients and CBT clinicians will not be blinded to group assignment.

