### Analyses

#### Sample size calculations

The sample size calculations were based on data from Hagen et al. [30] and the transition probabilities calculated for the intervention group in that study. The sample size was based on the transition probabilities at 9 months, where approximately 40% of the individuals had returned to work. Hagen et al. [59] found that the effects were largest for the earlier period after the intervention. This is therefore an argument to use 40% off sick leave at 9 months as the most relevant measure for effect in this study. This was compared to a hypothesized 60% return to work (RR 1.5) as an adequate effect size. The sample size calculations were based on standard formulas for calculating sample size, for studies comparing binomial proportions using the statistical package "R" (Library Hmisc). This may increase the power of the estimates in the analyses, since the simpler method used for the calculation does not include in this issue. All calculations were based on a power of 80% and a significance level of 5%.

Separate sample size calculations for males and females were computed. The total number of individuals should be approximately N = 4*n, where n is the calculated sample size and 4 is the number of arms in the study. The total number of males should be N = 4*65 = 260 and the total number of females N = 4*81 = 324. If we control for gender in the analysis instead of performing stratified analyses, we do not need to calculate separate sample sizes for men and women. The total number of participants should be 97 in each arm (N = 388). These numbers require a multi-centre design.

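### Combining clinics depends on an undefined centre effect judged on outcome data; clinics should always be pooled and clinic accounted for, as the randomisation is stratified by it.

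*Protocol article*

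**What the plan says.** All places are in the protocol article.

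- **Randomization:** "The list is stratified by clinic and gender".
- **Primary analyses of efficacy, pooling:** "The outcome from the participating clinics will be combined if no gross center effect is found". The article does not say how large an effect counts as gross, how it is assessed, or what is done if one is found.
- **Primary analyses of efficacy, regression models:** "Explanatory variables (treatment) and confounders (e.g. age, gender) will be included as in any regression model". Clinic is not named.
- **Primary analyses of efficacy, proportions:** "The proportions of participants with a positive primary outcome will also be compared across the treatment groups". No adjustment or stratification is stated.
- **Sample size calculations:** 97 per arm, 388 in all, for 40% against 60% return to work with 80% power at the 5% level. The figure rests on controlling for gender in the analysis rather than analysing men and women separately. The section adds that numbers of this size call for several centres.

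**The concern.** The pooling rule attaches the wrong condition to the primary analysis. Read in its usual sense, a centre effect means that clinics differ in their overall level of return to work. Because allocation is balanced within clinic by design, such differences do not bias the treatment comparison. They call for clinic to be in the analysis, not for the pooled result to be held back.

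The condition is also judged on outcome data and is left undefined, so whether there is one pooled answer becomes a judgement made after the outcomes are in. The branch in which an effect is found has no stated analysis. In the other branch, clinics are combined with no commitment to use a factor that shaped the randomisation. At stake are discretion in the primary analysis and, if clinics differ, some loss of efficiency.

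**Working it through.** **1. The plan's own figure.** Inputs from Sample size calculations: p0 = 0.40, p1 = 0.60, power 80%, significance 5% (taken as two-sided, which the article does not state).

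n = [1.960·√(2·0.5·0.5) + 0.842·√(0.4·0.6 + 0.6·0.4)]² / 0.20² = [1.386 + 0.583]² / 0.04 = 96.9, so 97 per arm and 4 × 97 = 388. This matches the article. The 97 is a per-arm total over all clinics, so the stated power presumes a pooled comparison.

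**2. Where the two stratification factors appear.**

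| | Clinic | Gender |
|---|---|---|
| Randomisation list | stratified | stratified |
| Sample size | pooled over clinics | controlled for in the analysis |
| Regression models | not named | named as an example |
| Comparison of proportions | none stated | none stated |

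The gap is mainly clinic. For gender it is limited to the comparison of proportions.

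**3. Effect on type I error of pooling without clinic.** The article gives neither the number of clinics nor their spread. Assume five equal clinics with evenly spaced control rates averaging 40%. The unadjusted test uses variance P(1−P) = 0.24 per patient. With allocation balanced within clinic, the true variance is 0.24 − V, where V is the between-clinic variance of the rates. The real two-sided error is then 2·[1 − Φ(1.96·√(0.24/(0.24 − V)))].

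- 30-50%: V = (2·0.10² + 2·0.05²)/5 = 0.005; critical value 1.96·√(0.24/0.235) = 1.981; error 0.048.
- 20-60%: V = (2·0.20² + 2·0.10²)/5 = 0.020; 1.96·√(0.24/0.22) = 2.047; error 0.041.
- 15-65%: V = (2·0.25² + 2·0.125²)/5 = 0.031; 1.96·√(0.24/0.209) = 2.10; error 0.036.

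**4. Simulation of the same setting.** Two arms of 97, 10 strata (five clinic levels × two), common odds ratio (0.6·0.6)/(0.4·0.4) = 2.25. The unadjusted two-proportion test is compared with a Mantel-Haenszel test over the strata.

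| Control rates | Type I error, unadjusted | Type I error, stratified | Power, unadjusted | Power, stratified | Gain in power points |
|---|---|---|---|---|---|
| 30-50% | 0.048 | 0.050 | 0.794 | 0.795 | 0.1 |
| 20-60% | 0.039 | 0.049 | 0.746 | 0.763 | 1.7 |
| 15-65% | 0.035 | 0.049 | 0.699 | 0.742 | 4.3 |

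The simulated errors agree with step 3. The fall of the stratified power below 80% comes mainly from the assumed spread, which shrinks the marginal difference (at 20-60%, 0.40 against 0.583). Only the last column is due to the choice of analysis.

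**5. Sensitivity.** A second simulation (4,000 runs per scenario) used six clinics with normally distributed log-odds and a gender log-odds difference of 0 or 0.5. With no clinic spread the gain is nil. With SD 0.6 it is about 2 points (0.744 against 0.760; 0.748 against 0.770). With SD 1.0, which puts clinics one SD either side of 40% at about 20% and 64%, it is 5 to 6 points (0.666 against 0.718; 0.646 against 0.702). The Monte Carlo standard error of each power is 0.006 to 0.008.

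**The case against.** - **The losses arise where the rule would probably not combine.** This is the strongest objection. With five equal clinics, an ordinary 5% between-clinic test detects a 20-60% spread with probability above 0.99 at N = 388. At 30-50%, where clinics might well be combined, the loss is negligible. A two-stage rule that stratifies only when such a test is significant stays within about 0.002 of always stratifying. This limits the size of the point, but the article does not state that two-stage rule: it says when clinics are combined and is silent on what follows otherwise.
- **An article condenses the full protocol.** A threshold, a fallback and a complete covariate list may stand elsewhere, and the covariates are given only as examples. This stands as far as missing detail goes. The point here is the conditional rule that the article does state.
- **The term is ambiguous.** It might mean treatment-by-clinic heterogeneity, which is worth examining. That can be reported without making the pooled analysis depend on it.
- **Discretion is limited.** Randomization blinds the trial statistician to group assignment, and differences in level can be judged without treatment codes. This is fair, although the article does not say that the check is done that way.

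A reader might infer that finding a centre effect means separate analyses by clinic, with power of only 16-37% (12 to 33 per arm if 3 to 8 clinics are assumed). The article never proposes that, and a clinic-adjusted model is equally compatible with its words. Nor does it support the reading that gender is neglected: it is a named covariate and is assumed to be controlled for in the sample size.

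**Conclusion.** The point holds in a limited form. Pooling is made conditional on an undefined feature of the outcome data, although the design stratifies by clinic and the sample size presumes pooling. Clinic is not committed to any primary analysis, and the comparison of proportions commits to neither factor.

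The certain gain from a change is less discretion. The statistical gain depends on assumptions that the article does not supply: about 0 power points at control rates of 30-50%, 2 to 4 points from 20-60% to 15-65%, and up to about 6 in the most heterogeneous scenario tried. Over the 20-60% to 15-65% cases, type I error returns from about 3.5-4% to 5%.

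It would be wrong to conclude that the rule inflates type I error: leaving clinic out makes the test conservative. It would also be wrong to insist on stratification alone, since clinic as a covariate or a random effect respects the design as well. The 97 per arm and the total of 388 stand.

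**What to change.** Replace the pooling sentence in Primary analyses of efficacy with:

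> All clinics are combined. The primary analyses, including the comparison of proportions, adjust for or stratify by clinic and gender whatever centre effect is observed. Treatment-by-clinic interaction is reported descriptively and does not alter the primary analysis. Any merging of very small clinics is fixed before unblinding.

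Clinic could enter the Cox model as strata, a covariate or a random effect. A Mantel-Haenszel analysis would serve for the proportions. The cost is wording only: both factors are known at randomisation, and the sample size does not change.

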#### Primary objectives

1) Are BI and CBT, and/or BI and seal oil, more effective than BI alone (BI and placebo) in increasing return to work, reducing health complaints, or both?

2) Are BI and CBT more effective than BI and seal oil, in increasing return to work, reducing health complaints, or both?

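### The NNT is estimated only after a significant result and against an arm identifiable only from the data, so it leans towards benefit and chance decides which contrast it describes

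*Protocol article*

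**What the plan says.** The section Primary analyses of efficacy first sets a comparison of all arms: "The proportions of participants with a positive primary outcome will also be compared across the treatment groups". The NNT follows from it under a condition: "If there are significant differences, we will estimate the number of participants". The quantity and its reference are then given as the "number of participants that need to be treated in order for one additional participant to benefit (NNT), compared to the least effective therapy". No arm is named at that point, and neither is the test that decides whether the differences are significant.

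The trial has four arms, listed under Randomization as "1) BI only, 2) BI and CBT, 3) BI and seal oil, or 4) BI and soy oil". Under Primary objectives, the first objective asks whether the CBT and seal oil arms are "more effective than BI alone (BI and placebo) in increasing return to work". The second asks: "Are BI and CBT more effective than BI and seal oil". The section on nutritional supplements treats soy oil as the placebo. Hypotheses of efficacy expects seal oil to have no influence on return to work or sick leave.

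**The concern.** This is a rule that the article states, not a detail it leaves out, and it selects on the observed results twice.

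- **The reference.** The arm with the lowest observed proportion is partly the arm with the worst luck. The minimum of several sample proportions is biased low, so a difference measured from it is biased high.
- **The condition.** If the NNT appears only when differences are significant, the trials that report one are those in which the observed differences came out large.

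The rule also leaves open which question the NNT answers. The primary objectives name their comparators in advance, whereas the NNT rule lets the data choose. If seal oil truly has no effect on sick leave, as the protocol hypothesises, it is as likely as BI only or soy oil to come out lowest. The NNT for CBT may then describe objective 2 rather than objective 1, for no reason but chance. At stake is whether the benefit expressed as an NNT can be taken at face value.

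**Working it through.** **Inputs from the protocol article (Sample size calculations).** Return to work 40% against 60%; power 80%; significance level 5%; 97 per arm, N = 388; four arms.

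**Step 1: reproduce the stated sample size.** Two-sided, pooled variance, no continuity correction:

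n = [1.960·√(2·0.5·0.5) + 0.842·√(0.4·0.6 + 0.6·0.4)]² / (0.6 − 0.4)² = 96.9, rounded up to 97; 4 × 97 = 388. This agrees with the article. The design difference of 0.20 corresponds to NNT = 1/0.20 = 5.0.

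**Step 2: bias from the lowest arm alone, by formula.** With three arms truly at 40%, the standard error of each proportion is √(0.4·0.6/97) = 0.0497. The expected minimum of three independent normal variables lies 3/(2√π) = 0.846 standard errors below their mean, so the reference is too low by 0.846 × 0.0497 = 0.042, about 4 points.

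**Step 3: simulate the stated rule.** 400,000 four-arm binomial trials per scenario, 97 per arm. Assumptions: the significance condition is an overall 3-df chi-square test at 5%, there is no dropout, and the arms other than CBT are at 40%. The CBT rate of 50% is also assumed. NNT is the reciprocal of the mean risk difference.

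| True CBT rate | True difference (NNT) | Condition met | CBT minus BI only, condition met | CBT minus lowest arm, condition met |
|---|---|---|---|---|
| 60% | 20 points (5.0) | 84% | 21.6 points (4.6) | 26.0 points (3.8) |
| 50% | 10 points (10) | 27% | 16.2 points (6.2) | 21.6 points (4.6) |

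Split by source, in points:

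- CBT 60%: the condition adds 21.6 − 20.0 = 1.6; the choice of lowest arm adds 26.0 − 21.6 = 4.4.
- CBT 50%: the condition adds 16.2 − 10.0 = 6.2; the choice of lowest arm adds 21.6 − 16.2 = 5.4.

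With all four arms at 40%, the condition is met in 5% of trials. In those, the best-minus-worst gap averages 20.1 points, an NNT of about 5, which is the design effect.

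**Step 4: which arm becomes the reference.** At the design rates, BI only, soy oil and seal oil are each lowest in about 33% of trials, with or without the condition. If seal oil were truly at 35% (assumed), it would be the reference in about 64% of the trials that meet the condition, and the CBT NNT would average 3.6.

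**Step 5: sensitivity to the assumed test.** If the condition is instead a pairwise 5% test of CBT against the lowest arm, the mean reported difference is 24.8 points (NNT 4.0) at a true 20 and about 19 points (NNT 5.2) at a true 10. For a fixed BI-only reference reported only when its own pairwise test is significant, the figures are 22.4 and about 18 points. The direction does not change, but the share due to the reference does.

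**The case against.** **The references are legitimate.** A reader might infer that the NNT could be set against an arm that is no proper comparator at all. The protocol does not support that. Objective 1 includes BI with placebo in its comparator, and soy oil is the placebo. CBT against seal oil is objective 2. At the design rates, every arm that could be lowest therefore matches a primary contrast for CBT, and in about two thirds of trials the reference is BI only or placebo. This stands. What remains is that chance picks the contrast, and that the lowest of several arms is a biased reference whichever arm it is.

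**Much of the inflation is ordinary selection on significance.** A reader might attribute the whole gap between a true NNT of 10 and a reported 4.6 to the comparator. That would be wrong: with a fixed BI-only reference and the same condition, the mean is already 16.2 points. Nor does the rule report an NNT in every trial: with no true effect it would do so in only 5%.

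**There is a reason to withhold an NNT.** When the interval for the risk difference includes zero, the interval for the NNT passes through infinity. The article also compares proportions across groups without any condition. Both points are fair. They argue for always giving the risk difference, not for leaving the NNT's reference open.

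**BI only may have been meant.** Possibly, but the text does not say so. If it was, naming the arm costs a few words, and the effect of the condition remains.

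**The NNT is a follow-on summary.** True. The transition models, the Cox model and the sample size do not depend on it.

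**Conclusion.** The point holds as a flaw in a stated reporting rule. The NNT is conditional on significance and measured from an arm that only the results identify, and both features favour benefit. Under the assumed overall chi-square condition with 97 analysed per arm, the average report is NNT 3.8 for a true 5.0, and 4.6 for a true 10. The choice of lowest arm accounts for about 4 to 5 points of the inflated difference, and selection on significance for the rest. The exact sizes rest on a test that the article does not name, on 40% in both oil arms, on no dropout, and for the second case on an assumed CBT rate of 50%.

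In about a third of trials at the design rates, the NNT would describe CBT against seal oil and so would not answer objective 1. A reader should not infer that soy oil or seal oil is an invalid comparator, or that the primary test or the sample size is compromised.

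**What to change.** Replace the NNT sentence in Primary analyses of efficacy with:

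> Absolute risk differences with 95% CI are reported for the prespecified contrasts of the primary objectives (BI+CBT vs BI only, with BI+soy oil as the placebo comparator also shown; BI+seal oil vs BI+soy oil; BI+CBT vs BI+seal oil), whatever the p-value. The NNT with 95% CI is derived from these; where the CI of the risk difference includes zero, the result is presented on the risk-difference scale.

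This removes the data-chosen reference. An NNT will still appear mainly where the interval excludes zero, but no estimate is withheld, because the risk difference and its interval are shown for every contrast. The cost is one sentence and a less favourable NNT. No new data or design change is needed.

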## Background

Muscle pain including low back pain (LBP) is common in the general population, and accounts for about 50% of the long-term sick leave in Norway. It is also among the most common reasons for frequent visits to the general practitioner [1]. Lack of knowledge related to the understanding of pain mechanisms, treatment strategies and management of back pain contribute to the problem [2]. The transition from normal complaints to prolonged illness and disability is poorly understood, but there are new studies suggesting augmented central pain processing [3]. This transition has recently been attributed to neurobiological and psychobiological sensitization mechanisms [4]. The theoretical and empirical background for this hypothesis has been developed in some detail. The main foundation is a general and systematic stress theory, the Cognitive Activation Theory of Stress, (CATS), developed from empirical data from human and animal studies [5].

The treatment principles for LBP and for other types of non-specific muscle pain, have changed over the last 15 to 20 years, from traditional treatments like bed rest and inactivity to more active treatment strategies ("The back pain revolution")[6]. Brief intervention programs have been demonstrated to be clinically beneficial and cost effective [7]. The prognosis for patients with chronic low back pain (CLBP) is poor when the condition has lasted over an extended period of time [8,9].

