### Evidence based treatments for LBP

The treatment principles applied in this study follow the evidence-based guidelines for the treatment of CLBP, developed in Europe (http://www.backpaineurope.org)[27]. The recommended treatments include conservative treatments like CBT, supervised exercise therapy, brief educational interventions (BI), and multidisciplinary bio-psychosocial treatments. A recent review of psychological treatments for CLBP, provide support for the efficacy of psychological interventions, including CBT, among persons with CLBP [28]. While the evidence points to BI and CBT as effective treatments, many of the studies included in the review, are at risk of bias because of methodological problems, and it has been argued that confidence in the results are unwarranted [29]. BI's are associated with positive outcomes for return to work early in the process [30]. However, it is still unclear whether the effect would be as beneficial later on, when the patients may develop behavior that adversely affects their illness and recovery. Some studies have shown that CBT is effective in reducing pain, while other studies have shown beneficial effects on physical and mental function and sick leave rates, but not pain [31,32]. It is difficult to replicate studies and results of the effects of CBT, because the components of the therapy and the experience of the therapists vary, and the treatment protocols are rarely documented. The European Guidelines for treatment of chronic low back pain emphasize the need to evaluate the effectiveness of using CBT-therapists without formal training in clinical psychology. These issues will be addressed and answered in the current trial; the CBT treatment protocol will be documented in a manual, and the treatment will be monitored closely. Therapists with different professional backgrounds will be recruited, trained, and followed in order to apply the protocol.

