### Inclusion criteria

1) Sick leave due to LBP for 2-10 months

2) At least 50% sickness compensation

3) Both participant and clinician agree that randomization is acceptable

4) Written informed consent from the participant

5) At least 50% employed

6) One of the following ICPC diagnoses: L02, L03, L84, or L86

7) Age between 20 and 60 years

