### Measures

#### Primary outcome measures

The main outcome in the study is sick leave. The data on sick leave/insurance status will be based on register data from the Norwegian National Insurance Administration.

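### Minor suggestion: name sick-leave duration at entry as a pre-specified covariate in the primary models, since patients enter after 2 to 10 months on sick leave

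*Protocol article*

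**What the plan says.** All places are in the Protocol article.

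- **Entry window** (Inclusion criteria): "Sick leave due to LBP for 2-10 months". The longest permitted spell is five times the shortest.
- **Prognosis** (Background): "The prognosis for patients with chronic low back pain (CLBP) is poor when the condition has lasted over an extended period of time".
- **Stage and the brief intervention (BI)** (Evidence based treatments for LBP): after noting good return-to-work results early in the process, "However, it is still unclear whether the effect would be as beneficial later on".
- **Stratification** (Randomization): "The list is stratified by clinic and gender".
- **Outcome** (Primary outcome measures): "The main outcome in the study is sick leave", taken from the national insurance register.
- **Covariates** (Primary analyses of efficacy): "Explanatory variables (treatment) and confounders (e.g. age, gender) will be included as in any regression model". A later sentence adds: "Possible changes in diagnosis and other characteristics will be built in".
- **Planning rate** (Sample size calculations): "The sample size was based on the transition probabilities at 9 months, where approximately 40% of the individuals had returned to work". This is set against a hypothesised 60%, a risk ratio of 1.5, with 97 per arm.

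The primary analysis is described as risks of moving between states of sick leave, disability pension and recovery. A Cox model is given as a possibility, transition-probability regressions are planned, and proportions are compared as well.

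**The concern.** The outcome is exit from sick leave, and duration at entry is the time a patient has already spent in that state. If longer spells lower the chance of returning to work, duration is a natural covariate for the primary models. The document's own argument for the trial leans on stage of illness, yet its examples of covariates are age and gender. Duration must be known for every patient, because eligibility depends on it.

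Two things are at stake, both modest. One is efficiency: time-to-event and transition models lose some power when a strong predictor is left out. The other is pre-specification: with an open covariate list, a decision to adjust for duration could be taken after an imbalance between arms has been seen.

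**Working it through.** **1. The plan's own sample size.** Inputs from Sample size calculations: 40% v 60%, 80% power, 5% significance (taken as two-sided). With pooled variance and no continuity correction,

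n = [1.96·√(2·0.5·0.5) + 0.842·√(0.4·0.6 + 0.6·0.4)]² / 0.20² = (1.386 + 0.583)² / 0.04 ≈ 96.9, so 97 per arm and 4 × 97 = 388.

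This matches the stated figure, which does not depend on a duration covariate.

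**2. Assumptions for what follows.** The document gives neither the distribution of duration nor the strength of its effect. Duration is taken as uniform over 2 to 10 months, and the strength is varied.

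**3. Comparison of proportions.** 4,000 simulated two-arm trials per row, 97 per arm, marginal rates held at 40% v 60%, logistic regression with and without duration.

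| Odds ratio for return, month 2 v month 10 | Control return, month 2 / month 10 | Power unadjusted | Power adjusted |
|---|---|---|---|
| 1 | 40% / 40% | 79.9% | 79.5% |
| 2 | 48% / 32% | 80.0% | 80.0% |
| 4 | 57% / 25% | 80.6% | 81.4% |
| 9 | 66% / 18% | 80.9% | 83.2% |

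Type I error is 4.3% to 5.4% throughout, with or without adjustment. The mean unadjusted risk difference is 0.198 to 0.201 against a true 0.20, so omission causes no bias. The adjusted log odds ratio is larger (0.91 v 0.82 in the last row) because the odds ratio is non-collapsible.

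**4. Cox model.** Exponential times to return, 97 per arm, follow-up of 12 months. The baseline hazard and treatment hazard ratio are set so that average return at 9 months is 40% v 60%. With no gradient the hazard ratio is ln(0.4)/ln(0.6) = 0.916/0.511 = 1.79; with a gradient it must be larger.

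| Hazard multiplier per extra month | Control return at 9 months, entry at month 2 / month 10 | Power unadjusted | Power adjusted | Gain |
|---|---|---|---|---|
| 1.0 | 40% / 40% | 86% | 87% | 1 |
| 0.9 | 54% / 28% | 87% | 88% | 1 |
| 0.8 | 69% / 18% | 87% | 93% | 6 |
| 0.7 | 84% / 10% | 86% | 97% | 11 |

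A second run of 2,000 trials per row gave 87/87, 88/90, 86/93 and 86/97, so differences of a point or two are simulation noise.

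If the hazard ratio is instead held at 1.79 under every gradient, the two steep rows become 80% v 88% and 67% v 85%. The treated arm then falls short of 60%, so this is no longer the planned effect.

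**5. Chance imbalance.** SD of a uniform duration = 8/√12 = 2.31 months. Standard error of the difference between two arms = 2.31·√(2/97) = 0.33. The 95% range is ±1.96 × 0.33 = ±0.65 month. At a multiplier of 0.8, a 0.65-month imbalance corresponds to a factor of about 0.8^(−0.65) = 1.16 in the hazard. The type I error already allows for such imbalances, but a single estimate can be moved by one.

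**The case against.** The case against has real force.

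- **The list is open.** Age and gender are examples, and other characteristics are mentioned. A reader might infer that the models treat a month-2 and a month-10 entrant as alike apart from age and gender. The text does not say so. It also fixes no time origin for the models. This objection stands.
- **The analysis plan is not shown.** A full covariate list is commonly left to it, so nothing is missing here. This stands too. What remains is a suggestion about one specific baseline value.
- **The document does not itself call sick-leave duration prognostic.** Background speaks of how long the chronic condition has lasted. Predictors of outcome does not list sick-leave duration. The spell is a close proxy for illness duration, and no more than that can be claimed.
- **The doubt about BI later in the course concerns effect modification.** Every arm receives BI, so it does not bear directly on the randomised contrasts. It supports an exploratory look only.
- **Low power.** A reader might carry the risk ratio of 1.5 over as a hazard ratio and conclude that power is only about 42% to 59%. That misreads the plan: with exponential times, a hazard ratio of 1.5 gives at most 1 − 0.6^1.5 = 53.5% return in the treated arm, short of the planned 60%. At 40% v 60% the unadjusted Cox model has 86% to 87%.
- **Bias towards no effect.** A reader might infer this from the smaller unadjusted hazard or odds ratio. Marginal and conditional ratios are different quantities, and the unadjusted test keeps its level.

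**Conclusion.** The point holds as a minor suggestion. Entry spans 2 to 10 months of sick leave, the strata are clinic and gender, and the only covariates given as examples are age and gender. Naming duration would cost almost nothing and could help. At the planned effect the gain in Cox power is about 0 to 1 points with no or a mild gradient and about 6 to 11 points with a steep one; for the comparison of proportions it is about 0 to 2 points. These figures rest on an assumed uniform duration, assumed gradients and exponential times. The documents do not support calling the omission an error, a source of bias or a sign of an underpowered trial. The unadjusted intention-to-treat analysis is valid, and the wording already permits the adjustment.

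**What to change.** In Primary analyses of efficacy, add one sentence: the duration of the current sick-leave spell at randomisation, as a continuous variable, is a pre-specified covariate in the primary Cox and transition models. State that the resulting hazard ratio is conditional on duration. Present the treatment effect by duration at entry as exploratory; this fits the secondary objective on baseline factors that predict outcome in the different groups.

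The cost is one degree of freedom. Duration is already known from eligibility. Stratification, sample size and trial conduct stay as they are.
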